### Sample Size

In this pilot study, the sample size was estimated according to the grade (Gr) of the Radiation Therapy Oncology Group (RTOG) (Cox et al., 1995) and National Cancer Institute (NCI) (Trotti et al., 2000) for the RID reported in the relevant literature. Kong et al. (Kong et al., 2016) investigated the incidence rate of RTOG Gr ≥ 2 in breast cancer patients with RID using Jaungo, which is the primary outcome in this study, at 46.7%. For non-steroidal moisturizer, there was no primary report using RTOG grade, but the incidence rate of NCI Gr ≥ 2 of RID in breast cancer patients was 9.0% (Leonardi et al., 2008). Clinically, the RTOG and NCI are common assessment grading tools, and each value of the incidence rate is compatible. Therefore, we estimated the incidence rates of the Jaungo and the moisturizer groups to be 0.467 and 0.09, respectively. The formula for calculating the sample size is as follows:$$n_{c}=\;\frac{\left(1+\lambda \right)\sigma^{2}{\left(Z_{\alpha /2}+Z_{\beta }\right)}^{2}}{\lambda d^{2}}$$

At the 5% significance level, considering an estimated withdrawal rate of 15%, a total of 50 participants, 25 in each group will be required to achieve 80% power.

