#### Drop-Out Criteria

Any patient who meets one of the following conditions will be dropped out from the trial. 1) The subjects or their families withdraw consent to participate in the trial; 2) a violation of the inclusion/exclusion criteria is found during the trial; 3) a significant adverse event appears in the subject and/or it is difficult to continue the trial due to an adverse reaction; 4) any violation of the study protocol; 5) the compliance level of the intervention (Jaungo or moisturizer) is less than 70%; 6) subjects who take medications, etc. that may affect the results of this study without confirmation from the attending physician; 7) any cases that the attending physician judge as inappropriate to the trial; 8) subjects who pregnant during the trial period; 9) subjects who fail to follow up during the trial period; 10) subjects who died during the trial period.

The methods used to contact the subject must be recorded in the supporting documents in the case of subjects who fail to follow up to prove that reasonable efforts were made to contact them. The patients who dropped-out due to significant adverse events could be provided with appropriate treatment for side effects. In these cases, the attending physician shall continuously evaluate the subjects until the adverse reactions are resolved or determined to be permanent.

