#### Intervention

The research will be conducted for a total of 7–9 weeks with nine individual assessments, consisting of topically administrating the Jaungo (Hanpoong Pharm & Foods Corporation, Seoul, South Korea) or the moisturizer (X-derm^®^, Pharmbio Korea Corporation, Seoul, South Korea) for the period of RT, 5–7 weeks, through eight visits after screening and a follow-up 2 weeks after the end of the application. The participants assigned to the Jaungo group will apply Jaungo on the entire irradiated skin region three times a day from the first day of RT, with a 1 cm distance from the skin marking line. The moisturizer group will apply the moisturizer in the same process.

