### Data Collection and Management

The participants will visit the outpatient clinic every week with a 3-day visit window during RT and 2 weeks after the end of RT. Figure 2 shows the study procedure and outcome measurements.

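### Drop-out item 4 removes a patient for any protocol violation, which leaves item 5's 70% threshold without effect and can cut short outcome data that the ITT-based analysis relies on

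*Protocol article*

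**What the plan says.** The Drop-Out Criteria open with a mandatory rule: "Any patient who meets one of the following conditions will be dropped out from the trial". Ten conditions follow. Two of them read "4) any violation of the study protocol; 5) the compliance level of the intervention (Jaungo or moisturizer) is less than 70" per cent. Item 6 covers medication that could influence the results and was not cleared with the attending physician. The only evaluation after drop-out that the section describes is follow-up of adverse reactions until they resolve or are judged permanent.

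The conduct against which a violation would be judged is demanding. The Intervention section has patients apply the product "three times a day from the first day of RT", over an RT course of 5–7 weeks. Data Collection and Management schedules visits "every week with a 3-day visit window during RT".

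The Statistical Analysis section starts from the ITT set and takes out three groups only: eligibility violators, patients who never used the product, and patients with no data after screening. Outcome Measurement grades RID by RTOG at every visit during RT and 2 weeks after it. The primary outcome is the incidence of grade 2 or higher.

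The Sample Size section arrives at 50 patients for 80% power, "considering an estimated withdrawal rate of 15" per cent.

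**The concern.** Items 4 and 5 set different tolerances for the same behaviour. A missed application departs from the three-times-daily schedule, so item 4 catches it at once, while item 5 acts only when compliance falls below 70%. Since any one condition suffices, the stricter item decides and the threshold in item 5 has no effect. The qualifiers in item 6 are overridden in the same way.

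The second conflict is with the analysis. The analysis set keeps violators and low compliers, but the drop-out rule takes them out of the trial. The primary outcome accumulates over the whole RT course and 2 weeks beyond it. If grading ends at drop-out, a patient who would later have reached grade 2 is recorded without that event. The primary outcome is then incompletely observed for reasons unrelated to safety or consent.

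**Working it through.** **1. Items 4 and 5 side by side.** Assuming application on every calendar day of RT, 5–7 weeks is 35–49 days, and 3 × 35 = 105 to 3 × 49 = 147 applications. Compliance of at least 70% allows 0.30 × 105 = 31.5 to 0.30 × 147 = 44.1, so 31 to 44 missed applications. Item 4, read as written, allows none. Every patient caught by item 5 has already been caught by item 4.

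**2. Drop-out rule against analysis set.**

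| Patient | Drop-Out Criteria | Statistical Analysis |
|---|---|---|
| Eligibility violation | dropped (item 2) | excluded |
| Other protocol violation, product used, some data | dropped (item 4) | kept |
| Compliance below 70%, product used, some data | dropped (item 5) | kept |

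The last two rows are the conflict. The number analysed does not fall, but the outcome record of those patients may be incomplete.

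**3. The plan's own sample size.** Inputs from the Sample Size section: "we estimated the incidence rates of the Jaungo and the moisturizer groups to be 0.467 and 0.09, respectively"; 5% significance (two-sided, from Zα/2 in the formula); 80% power; 15% withdrawal. The usual two-proportion formula, with pooled variance under the null and without continuity correction, is

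n = [z₀.₉₇₅ √(2p̄(1−p̄)) + z₀.₈₀ √(p₁(1−p₁) + p₂(1−p₂))]² / d².

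Here p̄ = (0.467 + 0.09)/2 = 0.2785 and d = 0.377.

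- Null term: 1.960 × √0.4019 = 1.2425.
- Alternative term: 0.8416 × √0.3308 = 0.4841.
- n = (1.7266)² / 0.1421 = 20.97, so 21 per arm.
- 21 / 0.85 = 24.7, so 25 per arm and 50 in total.

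This matches the stated total. The formula as printed, with one variance σ², gives 28 per arm with pooled variance or 23 with averaged unpooled variance (each rounded up before and after inflation), so the match is to the standard two-proportion version.

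**4. Power if outcomes were lost.** Power = Φ[(d√n − 1.2425) / √0.3308], with n = 25 × (1 − total loss) per arm. The loss rates are assumptions, because the documents give none. At 20% loss, n = 20: (0.377 × 4.472 − 1.2425) / 0.5752 = 0.771, so 78.0%.

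| Total loss | n per arm | Power |
|---|---|---|
| 0% | 25 | 86.8% |
| 15% | 21.25 | 80.5% |
| 20% | 20 | 78.0% |
| 30% | 17.5 | 72.0% |
| 50% | 12.5 | 56.2% |

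At 21 per arm (4/25 = 16% loss) power is 80.05%, so on this approximation it falls below 80% once fewer than 21 per arm remain. Exact enumeration of the uncorrected chi-squared test gives 83.3% at 21 per arm, 80.8% at 20, 78.2% at 19 and 71.7% at 17.

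**5. If patients stay in but events are missed.** Suppose 20% of each arm were dropped before reaching grade 2 and counted as event-free. The expected difference would shrink from 0.377 to 0.377 × 0.80 = 0.302. The 20% is again an assumption, and the article does not say how such patients would be counted.

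**The case against.** A reader might infer that item 4 makes 80% power impossible and contradicts the 15% allowance. The documents do not support that. The 15% is a planning estimate, which a conduct rule can make optimistic but cannot contradict, and no violation rate is given to show that it would be exceeded. Nor does drop-out under item 4 reduce the number analysed, because the Statistical Analysis section keeps violators who used the product and gave data. By the exact calculation, power is still 80.8% at 20% loss.

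A reader might also infer that most of the sample would be dropped for trivial lapses, a vitamin tablet included. The Prohibited Concomitant Medications section lists vitamins as self-treatment among treatments related to RID, so a vitamin taken for another reason is not plainly a violation. A share as large as most of the sample would need per-application miss rates that the documents do not give.

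Selective removal by arm is a further tempting inference. Participants know their product, but Randomization and Blinding says that the principal investigator and sub-investigator are blinded and the assessors independent. The article shows no clear route to arm-dependent dropping by them.

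Finally, the specific compliance rule in item 5 could be taken to govern missed applications, with item 4 as a catch-all for other breaches, and a full protocol may define which violations count. That is a sensible reading, but it is not what the list says: any one condition triggers removal and item 4 carries no limit. It also leaves the conflict with the analysis set in place. The article does not say that RTOG grading stops at drop-out, so truncation is a risk and not an established fact. However, continued evaluation is described only for adverse events.

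**Conclusion.** The point holds as a conflict in the stated rules. Item 4 as written makes item 5 redundant, and it removes from the trial patients whom the ITT-based analysis set retains. The main consequence is incomplete ascertainment of the primary outcome: a grade 2 or higher reaction after drop-out could go unrecorded. Its size cannot be determined from the documents.

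The effect on power is conditional. It needs dropped patients to lose their primary outcome, and total loss to exceed about 16% (normal approximation) or 20% (exact test). The figures take the protocol's planning rates of 46.7% and 9.0% as given; whether those rates are sound is a separate question, not examined here. The point warrants a short amendment. It does not show that the design fails.

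**What to change.** Reconcile items 4 and 5 with each other and with the Statistical Analysis section:

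- Delete item 4, or limit it to a short named list of violations that make a patient's trial data unusable, such as absence of valid consent.
- Log every other deviation without removing the patient from the trial.
- Continue the scheduled RTOG assessments through 2 weeks after RT for every randomised patient who has not withdrawn consent. This concerns outcome assessment only; whether a patient goes on using the product is a separate clinical matter.
- If item 4 stays as printed, revisit the 15% allowance and the stated power to match it.

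The cost is a brief amendment and the remaining scheduled visits for patients who would otherwise have been dropped. The downside is that imperfectly adherent patients remain in the data, as an ITT-type analysis expects.

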### Randomization and Blinding

Patients who have agreed to the trial will be screened on the day of screening (visit 0) whether they meet the inclusion/exclusion criteria. The enrolled participants will be randomly allocated to two parallel groups with a 1:1 ratio at the date of visit 1; either the Jaungo group or the moisturizer group. The random number will be generated by an independent statistician using a 2 × 2 randomized permuted block design. Each piece of paper with the allocation group information according to the random number will be sequentially inserted into an opaque envelope and sealed. After the screening, the enrolled participants will open the envelopes in order and will thus be assigned to either the Jaungo group or the moisturizer group.

Throughout the study process, the clinical research coordinator is responsible for recruiting participants, screening, and assigning random assignments. This trial is a single-blinded study because each intervention can be distinguished differently from the participants. The statisticians and envelope processors, group allocators, management pharmacists, and outcome assessors for the clinical trial are all independent. Additionally, the principal investigator and sub-investigator will be blinded to the assigned group.

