### Outcome Measurement

The participants will be assessed at every visit during RT and 2 weeks after the end of RT. The assessment will be conducted by radiation oncologists who do not know which group the participant belongs to, and will be single-blinded. The date of the occurrence and severity of RID will be evaluated at every visit from the start to end of RT and 2 weeks after, based on the RTOG grade. An incidence rate of Gr ≥ 2 RID will be recorded as the primary outcome of this study. At the start and end of RT and 2 weeks later, the quality of life (QOL), skin reaction symptoms, and maximum pain related to RID will be measured based on the Catterall skin scoring profile (CSSP) (Catterall et al., 1971), the Korean version of Skindex-29 (Ahn et al., 2004), and numeric rating scale (NRS) (Haefeli and Elfering, 2006). The maximum grade of RID, time to onset of RID, the value of CSSP, the Korean version of Skindex-29, and NRS, and the types and frequencies of adverse events will be compared as secondary outcomes between the two groups.

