### Statistical Analysis

The collected data will be statistically assessed using SPSS Version 25.0 (Chicago, IL), based on the intention-to-treat (ITT) set, except for the following subjects: 1) subjects who violate the inclusion/exclusion criteria; 2) subjects who have never used the intervention medication; and 3) subjects who have not provided any data after screening. The demographic characteristics of all participants will be reported as the mean and 95% confidence interval (95% CI) for continuous variables or frequencies and percentages for categorical variables. The incidence rate of RTOG Gr ≥ 2 RID, the primary outcome of this study, will be evaluated the difference between two groups using the Chi-squared test. Among the secondary outcomes, the maximum grade of RID based on RTOG will be analyzed by Chi-squared test, the time to RID occurrence by Kaplan-Meier analysis, and the CSSP, Skindex-29, and the maximum NRS for RID-related pain by independent sample t-test or Mann-Whitney U test, depending on the normal distribution, to compare the differences between the two groups. Adverse events will be presented as descriptive statistics by dividing according to the severity of each intervention and adverse symptoms. The types and frequencies of adverse events determined to be causative of the intervention will be separately analyzed and reported. Differences will be considered statistically significant when *p* < 0.05. Adverse reactions will be presented as descriptive statistics, divided according to the severity of each group and each adverse event. The symptoms and frequencies of adverse reactions related to the intervention medication will be analyzed separately.

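### Drop-out item 7 lets the attending physician take any randomised patient off the trial with no stated trigger, and no RTOG grading is described afterwards, so primary events can go unrecorded

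*Protocol article*

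**What the plan says.** The Drop-Out Criteria section of the protocol article lists ten conditions under one lead sentence: "Any patient who meets one of the following conditions will be dropped out from the trial". Item 7 is "any cases that the attending physician judge as inappropriate to the trial". It carries no event, threshold or second check. Eligibility violations, adverse events, protocol violations, low compliance, other medication and pregnancy have items of their own, so item 7 covers what is left.

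After drop-out the section describes one kind of evaluation, for patients who left because of a significant adverse event: "the attending physician shall continuously evaluate the subjects until the adverse reactions are resolved or determined to be permanent".

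On blinding, Randomization and Blinding states that "the principal investigator and sub-investigator will be blinded to the assigned group". Outcome Measurement adds: "The assessment will be conducted by radiation oncologists who do not know which group the participant belongs to". The list of independent roles reads: "The statisticians and envelope processors, group allocators, management pharmacists, and outcome assessors for the clinical trial are all independent". The attending physician appears in none of these three statements.

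Outcome Measurement grades dermatitis by RTOG at every visit from the start to the end of radiotherapy and 2 weeks later, and makes the incidence of grade 2 or higher the primary outcome. The Statistical Analysis section works "based on the intention-to-treat (ITT) set" with three exclusions, and an item 7 drop-out is not one of them. The primary test is a chi-squared test.

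**The concern.** Item 7 operates after randomisation and rests on judgement alone. The lead sentence ties it to leaving the trial. Applied as written, a patient who has not yet reached grade 2 can be released, and nothing in the article provides for grading that patient again. If the judgement is influenced by how the skin is reacting, the missing grades are related to the outcome.

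The analysis set does not solve this. An item 7 drop-out stays in the ITT-based set, but that set then needs grades that were never taken. An analysis plan can choose how to treat missing grades; it cannot restore them.

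The decision could also be influenced by knowledge of the arm. The protocol says "This trial is a single-blinded study because each intervention can be distinguished differently from the participants", and the attending physician deals with these patients' adverse reactions. If removals of would-be events fell more in one arm, the comparison would be biased towards that arm. With 25 patients per arm, two or three removals can matter.

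**Working it through.** **1. The plan's own figure.** Sample Size gives rates of 0.467 and 0.09, a 5% level, 80% power and 15% withdrawal. The standard two-sided formula with pooled variance under the null is

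n = [1.960 √(2·p̄·(1−p̄)) + 0.842 √(p1(1−p1) + p2(1−p2))]² / (p1−p2)²

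With p̄ = 0.2785, the first term is 1.960 × √0.4019 = 1.243 and the second is 0.842 × √0.3308 = 0.484. So n = 1.727² / 0.377² = 2.981 / 0.1421 ≈ 21 per group. Then 21/0.85 = 24.7, or 25 per group and 50 in total. The stated size reproduces. The withdrawal allowance is 0.15 × 25 = 3.75, about 4 patients per arm from all causes.

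**2. What the text supports.**
- Consequence of item 7: leaving the trial (lead sentence of Drop-Out Criteria).
- Grading afterwards: none described; only safety follow-up of adverse-event cases.
- Period over which the primary event can occur: to 2 weeks after radiotherapy (Outcome Measurement).
- Analysis set: item 7 patients are not excluded (Statistical Analysis).
- Blinding of the person who decides: not stated.

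A grade 2 event already recorded before removal is kept. The loss concerns patients removed before their event.

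**3. Illustration of size.** Assumptions not in the documents: the same true rate p in both arms; a fraction f of would-be events removed before grading, in one arm only; a Pearson chi-squared test without continuity correction; rejection above 3.84. Rejection probabilities come from exact enumeration of the two binomial counts.

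- Counted event-free: recorded rate = p(1−f), still 25 patients. For p = 0.467 this is 0.374 at f = 0.2 and 0.327 at f = 0.3.
- Out of the denominator: recorded rate = p(1−f)/(1−pf), which is 0.374/0.907 = 0.412 and 0.327/0.860 = 0.380, taken as 23 against 25 patients.

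Expected patients removed at p = 0.467: 25 × 0.467 × 0.2 = 2.3, and 25 × 0.467 × 0.3 = 3.5.

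| True rate, both arms | Handling | f = 0 | f = 0.2 | f = 0.3 |
|---|---|---|---|---|
| 0.467 | event-free, two-sided | 6.4% | 12.1% | 19.4% |
| 0.467 | event-free, favouring the affected arm | 3.2% | 11.5% | 19.2% |
| 0.467 | out of denominator, two-sided | 6.4% | 7.5% | 10.0% |
| 0.09 | event-free, two-sided | 4.5% | 4.6% | 5.1% |

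The third row depends slightly on how many patients remain: with 22 left at f = 0.2 it is 6.6%, and with 21 or 22 left at f = 0.3 it is 9.0% or 9.3%.

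**4. Sensitivity to how removal is expressed.** At a 9% rate, f = 0.2 is only 25 × 0.09 × 0.2 = 0.45 of a patient, which is why that row hardly moves. If instead two would-be events are always removed and counted event-free, the two-sided rate goes from 4.5% to 11.8% at 9%, and from 6.4% to 10.9% at 46.7%. At 9%, however, two patients are nearly all of the 2.25 events expected in the arm.

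**The case against.** **The decider may be blinded.** A reader might infer that an unblinded physician can choose whose outcome is completed. The article does not support that. In a single-centre trial the attending physician may be the blinded principal investigator or sub-investigator, and a condensed article need not define every role. This stands: unblinding and selective removal by arm are not shown.

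**Grading might continue.** The article does not forbid grading after drop-out, and Outcome Measurement speaks of assessing participants at every visit. But a patient dropped from the trial is not plainly still a participant, and the one follow-up provision that is written covers safety only. The gap in the text remains. The handling of missing grades may be in an analysis plan that is not shown and is not criticised here.

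**Item 7 is a customary clause and not the only route.** This largely stands. The loss comes from the lead sentence, which links all ten items to leaving the trial. Several other items could remove patients for outcome-related reasons, and item 4 (any protocol violation) is also broad. Item 7 is the clearest case because it names no trigger, but rewording it alone would leave the other routes open.

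**The size is assumption-driven.** This stands. The uncorrected test already rejects 6.4% of the time with no removals at 46.7%, so the excess over 5% is not all due to item 7. The larger figures need removed patients to be counted event-free, which the article never says. The 30% case would use nearly all of one arm's withdrawal allowance of about 4 patients on would-be events.

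**Conclusion.** The concern holds as a weakness in how the drop-out rule is written. An open judgement made after randomisation takes the patient off the trial, no RTOG grading is described afterwards, and the ITT-based analysis still needs those grades. Primary events up to 2 weeks after radiotherapy can therefore be lost for reasons related to the skin reaction.

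The documents do not establish that the attending physician knows the allocation or that removals would differ by arm. That is a risk only.

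The effect ranges from negligible (about 5% at a 9% rate, counted event-free) through modest (about 7.5% to 10.0% at 46.7%, removed patients out of the denominator) to material (12.1% to 19.4% at 46.7%, counted event-free). All of this rests on assumed removal fractions in one arm only. The point deserves an amendment mainly because the remedy is cheap and protects the primary outcome.

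**What to change.** Amend the Drop-Out Criteria so that a drop-out by physician judgement does not end outcome assessment. RTOG grading should continue at the scheduled visits and 2 weeks after radiotherapy, and the patient should stay in the analysis set. Apply the same to the other items short of withdrawn consent, loss to follow-up or death, subject to the three exclusions already in Statistical Analysis.

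Record the reason for each item 7 decision, and have it made or confirmed by a blinded investigator. If the attending physician is already one of the blinded investigators, one sentence saying so settles the blinding part.

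Decisions on product use stay with the clinicians and are not affected.

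The cost is a short amendment. The Radiation Therapy section has five fractions a week, so patients are on site during treatment, and the added burden is the 2-week visit and a few extra gradings of patients who would otherwise have been released.
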